## Abstract

**Background:**

Recurrent patellar instability incidence is 5.8/100,000 population, and recurrent dislocations are reported in the range of 15–80%. Recurrent instability is multifactorial and can be associated with disorder of limb alignment, osseous development, congruity of the patella in the trochlea and soft tissue static and dynamic constraints. The multifactorial aetiology makes management challenging, and a lack studies in a heterogeneous population with robust clinical outcomes compounds this further. The options for medial patellofemoral ligament (MPFL) reconstruction include autologous graft reconstruction with semitendinosus tendon, or synthetic polyester woven grafts. In theory, in the young active patient, the surgeon may wish to preserve the hamstring tendons to reduce postoperative morbidity to the patient, reduce delay in recovery from donor site morbidity and preserve the hamstring tendons. There have been no randomised controlled trials (RCTs) to date that directly compare autologous hamstring and synthetic reconstruction methods. This trial aims to assess the functional outcomes in those undergoing MPFL reconstruction with either autologous hamstring graft reconstruction, or a commercially available synthetic polyester open woven tape.

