## Background

Recurrent patellar instability incidence is 5.8/100,000 population, and reported recurrent dislocations are in the range of 15–80% [1, 2], with recurrence >50% after two dislocations [3]. Up to 55% of patients are unable to return to their pre-injury level of activity [4]. This can be particularly difficult to manage due to the multifactorial nature of patellar instability [3, 5], and a myriad of surgical options are described [6]. These include imbrication [7], repair by both open [8, 9], and arthroscopic techniques [10, 11] and reconstruction using a variety of graft options [9, 12–16].

The medial patellofemoral ligament (MPFL) is the most important restraint to lateral displacement of the patella from 0° to 30° of flexion, providing up to 60% of lateral patellofemoral stability [17]. MPFL insufficiency is present in 90% of acute, and 100% of recurrent, patellar dislocations [18]. Outcomes following MPFL reconstruction with autograft are reported as good to excellent, with increases in validated outcome measures for patellar instability, namely the Kujala score [3, 19–22].

Synthetic graft outcomes are also encouraging with studies reporting increases in Kujala outcome scores and patient-reported success rates of up to 94% [23–27]. One study reports the outcomes as being comparable to those of autograft reconstruction, with minimal need for revision intervention [25]. Stability is further enhanced when MPRL reconstruction is performed in combination with vastus medialis advancement compared to MPFL reconstruction alone [27].

Potential complications of MPFL reconstruction include re-dislocation, postoperative quadriceps dysfunction, adverse reaction to synthetic graft material, persistent pain and patellar fracture, but these risks are low and quoted as 5–10% [28–30]. Whilst multiple options are described, there is a paucity of clinical comparative studies. No study has compared autologous to synthetic graft reconstruction.

The objective of the current paper is to present a randomised controlled trial designed to investigate the difference, if any, between autologous semitendinosus synthetic graft MFPL reconstruction in patients with patellar instability.

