**Fig. 1 Fig1:**
[figure not shown]
Example template of recommended content for the schedule of enrolment, interventions, and assessments. BPII, Panff Patellar Instability Index; ACL QoL, Anterior Cruciate Ligament Quality of Life Score

Collected data will be kept in the hospital notes in a designated study sub-section. All data will also be held on a secure hospital-server shared drive, accessible only to those registered as trial investigators. Patients will be designated alphanumeric codes rather than be identified by personal details. Data will be entered by either the Principal Investigator or a member of the trial team, then checked and verified by one of the additional collaborating authors. Data monitoring will be performed by the study unit Research and Development (R&D) team and/or the Regional Ethics Committee at their discretion.

Changes in trial design will be conveyed to the study unit R&D Department and the REC for ethical review. Any changes to the trial protocol will also be reflected in the ISRCTN documentation.

The data analysis will be by an intention-to-treat protocol, which will minimize bias between the treatment arms, and demonstrate the efficacy of the intervention itself.

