### Intervention

The intervention will be reconstruction of the MPFL using either autologous gracilis or semitendinosus tendon, or synthetic open weave polyester tape (Neoligament, Leeds UK), with advancement of the vastus medius obliquitus (VMO). All surgery will be performed by the Principal Investigator, who is a consultant with significant specialist interest and expertise in soft tissue knee reconstruction, and who has performed significant numbers of both techniques. This will eliminate any learning curve between techniques. All patients will be reviewed preoperatively the by Principal Investigator to ensure eligibility for inclusion. Consent will be gained by the Principal Investigator or a suitably trained orthopaedic registrar, who is part of the clinical trial team.

Patients will undergo general anaesthetic for surgery. Routine intravenous antibiotic prophylaxis will be administered in accordance with local Trust policy. Patients will be positioned in a supine position with a high thigh-tourniquet. A side support is used to support the leg in 90° of flexion. Diagnostic arthroscopy will not be performed as all patients with evidence of an osteochondral lesion on preoperative MRI will be excluded from the study. Reconstruction using either a hamstring autograft or synthetic graft will be performed as per the surgeon’s default technique. Should there be a breach of the synovial lining, this will be repaired to ensure a purely extra-articular reconstruction is performed.

The autograft tendon will be harvested through an approximate 3-cm vertical incision over the pes anserinus with a vertical opening to the bursa and exposure and release of the tendon using a tendon stripper. The senior author’s preference is to use the gracilis tendon, unless it is of a poor quality, or if the patient body habitus requires a more substantial graft, then the semitendinosus tendon will be harvested instead.

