### Outcomes

The primary outcome will be to determine the patient-reported outcome score using the validated Kujala score [32]. This is a validated scoring system designed specifically for patellar instability [32]. Scores will be collated preoperatively, and at the pre-defined postoperative time points of 3, 6, 12, 18 and 24 months. This will be identical for both autologous and synthetic reconstruction techniques. Specifically, we will report the change in the Kujala score at these set time points and analyse the data for differences between surgical techniques to determine if one appears to be superior. This will demonstrate the efficacy of the treatments under investigation, and allow a meaningful statistical comparison between the treatment arms.

Additional secondary outcomes scores will also be reported. These will be collected at the same time points as the primary outcome score, preoperatively and then postoperatively at 3, 6, 12, 18 and 24 months. The outcome scores will include the Tegner Activity Level Scale [33], Lysholm Knee Score [34], the Banff Patellar Instability Index (BPII) [35] and the anterior cruciate ligament (ACL) Quality of Life Score [36]. These scores have been previously validated and are reliable in assessing ligamentous injuries of the knee and are commonly reported in studies of ligamentous reconstruction.

Other secondary outcomes will include the incidence of complications and all-reason revision surgery. Those patients lost to follow up will have their data included up to this point to allow for analysis at the set postoperative time points. The aim is to have data on medium-term outcomes at 2 years for all participants.

At each study-review time point, participants will be questioned about adverse events attributable to undergoing surgical reconstruction of the MPFL that they have experienced since their previous review. This will include graft rupture/failure, synovitis, persistent instability and reoperation/revision surgery.

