### Statistical analysis and trial end points

The intended data analysis will be on an intention-to-treat and per-protocol basis to demonstrate non-inferiority. This will allow bias between the treatment arms to be minimised, and demonstrate the efficacy of the intervention itself. Data analysis will be performed by one of the study investigators using SPSS v22 for Mac (IBM Inc., Armonk NY, USA), and will be verified by the local unit R&D department. Data will be tested for normality using the Shapiro Wilk test. Appropriate parametric and non-parametric tests will used accordingly.

Primary outcome measures will be compared between groups at set postoperative time points of 3, 6, 12, 18 and 24 months. Additionally, outcomes at these time points will be compared to preoperative baseline i.e. the analysis metric will be the change from preoperative baseline. This will allow calculation of change in patient-reported outcome scores at the set time points and the change in these reported scores over the study timeframe.

For primary and secondary outcome scores, the mean ± SD, median and range will be given for continuous data. For the secondary outcomes, the frequency of complications and all-reason revision will be recorded as a percentage and analysed by chi square analysis. For all tests, a *p* value <0.05 will be considered significant.

End points will be completion of the study timeframe (2 years), or further dislocation/all reason revision surgery. The trial will only be stopped should information become available that indicates that it is unethical to use synthetic grafts.

We propose to test non-inferiority using the intention-to-treat analysis set. No crossover of treatment arms will be allowed to occur as part of the protocol. Therefore, the study shall include all participants, as randomised. Patients will be reviewed at each specified time point as previously outlined. A single imputation model with last value carried over (LVCO) will be employed should patients drop out or be lost to follow up. The trial is designed to accommodate a 60% dropout rate, and still maintain a suitable sample size for meaningful statistical analysis.

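### The stopping sentence names synthetic grafts alone, so harm confined to the autograft arm has no stated route to a trial stop and harm from the shared operation has no clear one

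*Protocol article*

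**What the plan says.** The section on statistical analysis and trial end points states: "The trial will only be stopped should information become available that indicates that it is unethical to use synthetic grafts". The sentence just before it concerns individual patients and does not stop the trial: "End points will be completion of the study timeframe (2 years), or further dislocation/all reason revision surgery".

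Three other parts of the protocol article bear on this.

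- **Oversight** (Trial design, text after Figure 1): "Data monitoring will be performed by the study unit Research and Development (R&D) team and/or the Regional Ethics Committee at their discretion". Design amendments have their own route: "Changes in trial design will be conveyed to the study unit R&D Department and the REC for ethical review". Neither sentence mentions stopping.
- **Safety data** (Outcomes): at each review "participants will be questioned about adverse events attributable to undergoing surgical reconstruction of the MPFL". The question is put to all participants.
- **Recognised harms**: the Background says "Potential complications of MPFL reconstruction include re-dislocation, postoperative quadriceps dysfunction, adverse reaction to synthetic graft material, persistent pain and patellar fracture". The abstract gives as a reason for sparing the hamstrings that this may "reduce delay in recovery from donor site morbidity".

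The article contains no other trial-level stopping condition, interim analysis or termination clause.

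**The concern.** The word *only* turns a reasonable example into an exclusive rule, and that rule looks at one arm. The autograft operation has a step that the synthetic operation lacks: "The autograft tendon will be harvested through an approximate 3-cm vertical incision over the pes anserinus". The document itself acknowledges donor site morbidity. If serious harm emerged from the harvest, the rule as written would give no ground for stopping, because such harm says nothing against synthetic grafts. Harm from a step done in both arms would fit the wording only by argument.

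This is not a complaint about missing detail. A condensed article may leave monitoring boundaries, committee charters and thresholds to a fuller document. Here the sentence is present and shuts out other reasons. A fuller document could remove the problem only by contradicting it.

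At stake is the protection of patients not yet operated on, and whether the people monitoring the trial have a protocol that supports them if the safety problem lies on the autograft side.

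**Working it through.** There is no figure to reproduce. The check sets the stopping sentence against each kind of harm that the article recognises, and asks whether that harm could satisfy the condition as worded.

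| Kind of harm | Where the article recognises it | Could it meet the stated condition? |
|---|---|---|
| Reaction to synthetic material | Background, complications list | Yes, directly |
| Re-dislocation, quadriceps dysfunction, pain or fracture arising in the synthetic arm | Background, complications list | Yes, if judged to count against synthetic grafts |
| The same events arising in both arms from a shared step (the patellar drilling is described before the text divides by graft type) | Background; Intervention | Unclear: the wording concerns the graft, not the operation |
| The same events confined to the autograft arm | Background, complications list | No |
| Tendon harvest and donor site morbidity | Intervention; abstract | No |

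**Is there another route in the text?** The monitoring sentence gives the R&D team and the ethics committee discretion to monitor, but states neither a criterion nor an authority to stop. The amendment sentence sends design changes for ethical review and does not mention stopping. The end point sentence closes a patient's own course in the study. None of them supplies a second stopping condition.

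**Consistency.** Adverse events are collected in both arms. Under the literal rule, trial data can bear on stopping through the synthetic arm, perhaps through both arms together, but not through the autograft arm alone.

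**Scale.**

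- Patients in the arm without a stated route: 15 of 30 = 50% (Sample size section).
- The Background puts the risk of complications at 5–10%. *If* that range applies to the autograft arm, which the article does not say by arm, the expected number of affected patients is 15 × 0.05 = 0.75 to 15 × 0.10 = 1.5.
- The abstract has recruitment running from January to December 2018, about 12 months. Reviews are at 3, 6, 12, 18 and 24 months. The earliest 12-month review therefore falls at about January 2019, when recruitment is due to be over. On that timetable, only the 3- and 6-month reviews of earlier patients, and complications that surface between reviews, could lead to a stop that spares anyone surgery.

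**The case against.** Five points can fairly be made in defence of the plan.

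1. **Shared harm may be covered after all.** If the common operation proved unacceptable, implanting a synthetic graft by that operation would be unacceptable too. This stands in part. A reader might infer that shared harm can never trigger a stop; the wording does not go that far. It leaves shared harm unclear rather than excluded, and the argument does nothing for harm from the harvest.

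2. **Counting complications does not measure the gap.** Only one of the five complications in the Background is specific to synthetic material, and a reader might infer that the other four lie outside the rule. They do not: any of them, seen in the synthetic arm, could support a judgement against synthetic grafts.

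3. **The vastus medialis step is not a safe example of a shared step.** The Intervention section can be read as applying it to both arms, but its operative description ties the step to covering the tape. The point here does not rely on it.

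4. **The asymmetry has a rationale.** The sample size section defines the control group from autologous reconstruction and describes a non-inferiority design, so it is natural to watch the synthetic graft more closely. That explains why synthetic grafts are named. It does not explain why every other reason is excluded, and the Trial design section describes both techniques as accepted practice.

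5. **Oversight exists.** A reader might infer that the R&D team and the ethics committee are forbidden to stop the trial for autograft harm. The article does not say that its stopping sentence binds them, and they might act outside it. This stands, and limits the point to what the stated rule provides. It is still poor practice to depend on oversight bodies acting against the protocol's own wording.

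**Conclusion.** The point holds in a limited form. Taken literally, the stopping sentence gives no route to a trial stop for harm confined to the autograft arm, and no clear route for harm from the shared operation. It fits badly with the two-arm collection of adverse events and with the discretionary monitoring described elsewhere in the same article.

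The likely practical effect is small: 30 patients, a single operation each, about one year of recruitment, and roughly one expected complication in the autograft arm on the article's own range. The sentence affects no estimate, error rate or conclusion about the primary outcome. The reason to correct it is patient safety, at almost no cost.

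The conclusion rests on two assumptions: that *only* is meant as written, and that no fuller protocol text overrides it. If a fuller text does override it, the two need to be reconciled.

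**What to change.** Reconcile the stopping sentence with the monitoring text in the Trial design section and the adverse event text in the Outcomes section. Remove the exclusive wording and the restriction to one graft, so that safety information from either arm, or from outside the trial, can be considered by the R&D team and the ethics committee already named. Which findings would justify stopping is for the investigators and those bodies to decide; no criterion is proposed here.

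The cost is one amended sentence, sent through the ethical review and registry update that the article already sets out for protocol changes. It needs no new committee, threshold, visits, staff or patients, and the analysis is unchanged.

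### Carrying the last Kujala score forward, with up to 60% dropout accepted, puts early-recovery scores into the later comparisons and can bias the non-inferiority result in either direction

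*Protocol article*

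**What the plan says.** The Protocol article, under Statistical analysis and trial end points, names one method for missing follow-up: "A single imputation model with last value carried over (LVCO) will be employed should patients drop out or be lost to follow up". The same paragraph gives the analysis it serves, "We propose to test non-inferiority using the intention-to-treat analysis set", and the loss it tolerates: "The trial is designed to accommodate a 60% dropout rate, and still maintain a suitable sample size for meaningful statistical analysis". The section opens by naming a per-protocol analysis as well. Arms are compared at 3, 6, 12, 18 and 24 months on change from baseline, and no visit is named as primary.

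The Outcomes section describes lost patients differently: "Those patients lost to follow up will have their data included up to this point to allow for analysis at the set postoperative time points". Similar wording appears under Recruitment for patients who withdraw.

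On failure of the reconstruction, the statistical section says: "End points will be completion of the study timeframe (2 years), or further dislocation/all reason revision surgery". It also says "Patients will be reviewed at each specified time point as previously outlined", and Outcomes adds: "The aim is to have data on medium-term outcomes at 2 years for all participants".

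**The concern.** Kujala is measured five times after surgery because it is expected to change. Carrying the last value forward assumes that it stops changing when the patient leaves. A 3- or 6-month score would then stand as a 24-month score and be analysed as if observed.

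The 24-month difference between grafts becomes a mixture of late and early differences, weighted by how many patients left, when, and from which arm. In a non-inferiority trial, an estimate pulled towards zero favours the claim. The Abstract gives a reason to expect an early difference: sparing the hamstrings is meant to avoid donor-site morbidity and the slower recovery that follows. A temporary synthetic-arm advantage could therefore be carried into the 2-year result. With a different dropout pattern, the same rule could make an equivalent graft look worse.

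**Working it through.** **Inputs from the Sample size section.** Kujala 56.7 before and 86.8 after surgery; 15 patients per arm; attrition up to 60%; SD 7.2; a 10-point difference called clinically relevant. The article does not label 10 points a non-inferiority margin; using it as one below is an assumption.

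**1. The plan's own figures.** Expected rise: 86.8 − 56.7 = 30.1 points. Tolerated loss: 15 × 0.60 = 9 per arm, leaving 6, just above the minimum of 5 that the section states. At that limit, 9 of 15 values per arm at 24 months could be carried forward.

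**2. Equal dropout d in both arms.** The expected difference under the rule is

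(1 − d) × (24-month difference) + d × (average difference at last visit).

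For a true 24-month deficit of 10 points on the synthetic graft, the deficit shown is:

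| Dropout per arm | Last-visit deficit 7 | 5 | 1.5 | 0 |
|---|---|---|---|---|
| 20% | 9.4 | 9.0 | 8.3 | 8.0 |
| 40% | 8.8 | 8.0 | 6.6 | 6.0 |
| 60% | 8.2 | 7.0 | 4.9 | 4.0 |

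Example: 0.4 × 10 + 0.6 × 5 = 7.0. The 7-point column is the same recovery shape in both arms, with assumed fractions of final recovery of 0.40, 0.60, 0.85 and 0.95 at 3, 6, 12 and 18 months and departure equally likely after each visit (mean fraction 2.80 / 4 = 0.70). The 1.5-point column corresponds to a simulated curve with faster early synthetic recovery: (4.9 − 4.0) / 0.6 = 1.5.

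**3. Unequal dropout.** Let s be the average shortfall of the last observed score below the 24-month score. The expected difference is then

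(24-month difference) − (d_syn × s_syn − d_auto × s_auto).

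With the same fractions and a 30.1-point rise, s = 30.1 × 0.30 = 9.03.

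- No true difference, dropout 20% autograft and 40% synthetic: 0 − (0.4 × 9.03 − 0.2 × 9.03) = −1.8, a false deficit. Reversing the rates gives +1.8.
- True deficit of 10, so the synthetic rise is 20.1 and s_syn = 20.1 × 0.30 = 6.03, same dropout: −10 − (2.41 − 1.81) = −10.6. The deficit is slightly exaggerated.

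**4. Effect on the decision.** This was simulated with 15 per arm, SD 7.2, 40,000 runs, an assumed correlation between visits of 0.6, and non-inferiority declared when the lower two-sided 95% limit is above −10. With a true deficit of 10 and complete data, false non-inferiority is about 2.5%. With last values carried forward:

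| Dropout per arm | Same recovery shape | Faster early synthetic recovery |
|---|---|---|
| 20% | 3.5% | 7.5% |
| 40% | 5.1% | 17.7% |
| 60% | 6.9% | 33.2% |

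In the other direction, with no true difference and 20% v 40% dropout, the chance of showing non-inferiority falls from 96% to 67%. With equal 40% dropout it falls from 96% to 80%. With a true deficit of 10 and 20% v 40% dropout, false non-inferiority falls to 1.5%.

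**The case against.** Several stronger readings are tempting, and the article does not support them.

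- **That the rule always favours non-inferiority.** Step 3 shows otherwise. The direction depends on the timing and balance of dropout and on how the arms recover.
- **That it necessarily understates uncertainty.** Values from different recovery stages are mixed, so the simulated SD rose (from 7.1 to 9.3 with equal 40% dropout and no true difference) and power fell.
- **That a 10-point deficit would show as 4.** This needs both 60% dropout, which is a tolerated ceiling and not a forecast, and no difference at all at the last visit.
- **That failed grafts would be scored as good results.** The article ties the rule to dropout and loss to follow-up, not to re-dislocation or revision, and does not say that Kujala collection stops at those events. At the 5–10% complication risk quoted in the Background, 15 × 0.05 to 15 × 0.10 is 0.75 to 1.5 patients per arm. If pre-failure scores were carried forward, failure rates of 5% v 10% with an assumed 30-point loss would show a true −1.5 as −0.4, masking about 1 point. Revisions and complications are also compared as separate secondary outcomes.
- **That the Outcomes section flatly contradicts the rule.** It does not say that data are used only up to the point of loss, and it can be read as compatible with carrying forward. The wording is loose.

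It is also fair that 24 months is only one of five comparison points, and that sensitivity analyses commonly sit in an analysis plan that is not shown; their absence here is not held against the article.

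None of this rescues the rule. The article itself prescribes it for a score expected to rise by about 30 points. A bias whose sign depends on unknown dropout is a reason to replace the method.

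**Conclusion.** The point stands in this form: the prescribed single imputation would place early-recovery Kujala scores in the later comparisons, for up to 9 of 15 patients per arm at 24 months, and can move the between-arm difference either way. Under similar dropout with a deficit that emerges late, or faster early synthetic recovery as the article's own rationale suggests, it shrinks a true deficit and favours non-inferiority. A deficit of 10 that is half as large at the last visit shows as 9, 8 and 7 points at 20%, 40% and 60% dropout. More or earlier synthetic-arm dropout works against non-inferiority.

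The rise, the arm size and the 60% limit come from the article. The recovery curves, dropout timing, visit correlation and 10-point margin are assumptions, so the error rates are illustrations and not predictions.

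The end-points sentence supports a narrower conclusion. A reader might infer that follow-up ends at re-dislocation or revision and that the pre-event score is then carried forward, but the text leaves this open. The passages need reconciling.

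**What to change.** 1. Replace the carry-forward rule with a likelihood-based repeated-measures model of all observed Kujala scores at 3, 6, 12, 18 and 24 months, with baseline as covariate and a small-sample degrees-of-freedom correction. Multiple imputation is an acceptable alternative.
2. Add a sensitivity analysis that progressively worsens the missing synthetic-arm scores and reports whether the non-inferiority conclusion changes.
3. Reconcile the end-points sentence with the statement that patients are reviewed at every time point and with the aim of 2-year data on all participants. State whether Kujala is collected after re-dislocation or revision and how it is used, and that scores from before such an event are not carried forward as later results.
4. Align the wording on data up to the point of loss or withdrawal, in Outcomes and Recruitment, with the chosen method.

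The cost is wording in the protocol and analysis plan; the visits already exist. The model relies on missingness at random, which is why item 2 is needed. Precision at 15 per arm is limited: five visits with an unstructured covariance matrix need 5 × 6 / 2 = 15 covariance parameters, so a simpler fallback structure should be specified in advance.
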